### Ethical Considerations

The Mahatma Gandhi Ayurved College Hospital and Research Centre’s Institutional Ethics Committee approved this study (registration: MGACHRC/IEC/July-2022/521), and it was also registered with the Clinical Trial Registry of India (CTRI/2023/03/051135). The same ethical committee also approved the addition of the site at CSMSS Ayurved College, Chhatrapati Sambhajinagar. After receiving a No Objection Certificate from the institutional ethical committee of the CSMSS Ayurved College (AMCS/1407/2023), the participant recruitment at both sites will be initiated. The institutional ethical committee will decide on the end point and oversee the trial as it progresses. The researchers will assess any adverse events and will report to the ethics committee. Consent from parents and assent from patients (older than 12 years) will be obtained before conducting the trial in the local language while explaining every aspect of the study. Every participant will get information regarding the study’s design and objectives, data confidentiality, and the freedom to withdraw from the study at any moment without giving a reason. The informed consent form includes a patient information sheet (part 1) and a certificate of consent (part 2). Secondary analysis will be covered without additional consent. Data will be anonymized, and the personal information of the participants will be kept confidential before, during, and after the trial. Physical data will be stored in a protected storage facility, with access available only to the researchers. Computerized data will be held in a password-protected computer. Data access will be restricted to members of the research team only. During data analysis, measures will be taken to protect participants’ privacy. Participation in the study is completely voluntary; hence, no incentive will be provided to the participants. During the treatment period, if the patients’ condition worsens, the case will be excluded and will receive conventional treatment and care until the symptoms subside, free of charge. The ethics committee will be informed of the patient’s condition. The therapy will be discontinued, and the child will be withdrawn from the study if any other illness arises during the treatment period that could influence study outcomes. Similarly, if a participant experiences personal issues that prevent continuation of therapy and are likely to affect the study results, they will also be withdrawn. If the patient misses any of the periodic follow-ups during the intervention, they will be excluded from the study.

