## Methods

### Study Design

A randomized, standard-controlled, double-blind equivalence clinical trial will be performed. The study flow is depicted in Figure 1. The study participants required for the trial include children with overweight aged between 10 and 16 years of age will be selected from the Outpatient Department and Inpatient Department of the Department of Kaumarbhritya, Mahatma Gandhi Ayurveda College Hospital and Research Centre, Salod (H), and Chhatrapati Shahu Maharaj Shikshan Sanstha’s (CSMSS) Ayurved College and Hospital, Chhatrapati Sambhajinagar, based on the inclusion criteria.

Overweight (Sthaulya) children will be diagnosed as having a BMI greater than or equal to 23 and less than 27 kg/m^2^ [11]. Screening will include hemoglobin percentage, thyroid-stimulating hormone, and random blood sugar. A total of 88 diagnosed children with overweight will be selected after obtaining written informed consent from their guardians. Participants will be randomly divided into 2 groups by block randomization using a computerized random number generator or statistical software. Group A (control group) will receive Navak Guggulu, while group B (trial group) will receive Vachaharidradi Gana Vati orally (Table 1). Medications will be dispensed in opaque containers following the sequentially numbered, opaque, sealed envelope (SNOSE) technique to maintain allocation concealment. Both groups will receive counseling to perform 12 Suryanamaskara (Sun Salutation) per day and adhere to the dietary restrictions. Guardians will be educated and advised to support their children’s consistent participation in the interventions. All the baseline parameters will be recorded at the study’s initiation. The treatment duration will be 90 days, with follow-up assessments on the 15th, 30th, 45th, 60th, 75th, and 90th day to monitor progress and ensure adherence. Lipid profile will be assessed before treatment and on the 90th day of intervention to evaluate the efficacy of the interventions. An additional follow-up will occur on the 180th day to determine whether the intervention’s possible effects are lasting.

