### Participants

It is crucial to calculate the effect size according to the equivalence or superiority formula with the help of the SD and mean difference of the reference paper [44]. This approach enhances the RCT, making it superior to other types of research. In this study, an attempt is made to assess the equivalence effect of Vachaharidradi Gana Vati against the standard controlled drug, Navak Guggulu. The equivalence formula is applied, and the sample size is calculated to minimize any bias. So, the formula for equivalence (parallel design) has been used to calculate the sample size of this study. For that, the reference values of the control drug have been used [44].

The formula for equivalence (parallel design) is:

where *Z*_α_=1.96, α=type I error at 5%, σ=SD, *Z*_β_=0.84 (for equivalence 2-tailed), β=type II error at 20%, and δ=true differences in means.

Sample size (N) = *n*1 = 2 × (1.96 + 0.84)^2^ × (0.86)^2^/(0.57)^2^ = 39 each

Total=78 samples. With 10% dropout=43 each=86 samples.

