### Statistical Analysis

The statistical analysis will be performed at the end of the study. It will involve various tests to evaluate both within-group and between-group efficacy of Navak Guggulu and Vachaharidradi Gana Vati in managing Sthaulya (overweight) among children. For normally distributed continuous variables like BMI, WHR, and skinfold thickness, paired 2-tailed *t* tests will be used to evaluate the efficacy of each intervention within the same group (pre- and posttreatment comparisons).

For nonnormally distributed data, the Wilcoxon signed rank test will be used. For normally distributed data, independent 2-tailed *t* tests will be used for between-group comparisons of mean changes; for nonnormal data, the Mann-Whitney *U* test will be used.

To ensure valid comparisons, the analysis of covariance will be used to account for any potential baseline variations between groups. To evaluate residual efficacy after treatment discontinuation at 180 days, repeated measures ANOVA will analyze longitudinal changes in outcomes, while mixed-effects models will handle missing data or variability across time points. For stratified analysis based on Desha (geography), Kala (season), and Prakruti (body constitution), multivariate regression analysis will identify predictors of treatment efficacy, and interaction analysis will explore the influence of these factors. A statistician consultation will be considered for the selection of the proper statistical method.

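### Removing randomised children for one missed treatment-period visit, or for worsening, discards usable data, undermines the randomised equivalence comparison, and must be reconciled with the plan to model missing data

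*Protocol article*

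**What the plan says.** Ethical Considerations in the protocol article sets four rules that remove a child after randomisation:

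- Missed visit: "If the patient misses any of the periodic follow-ups during the intervention, they will be excluded from the study".
- Worsening during treatment: "if the patients’ condition worsens, the case will be excluded". The child then receives conventional care.
- Intercurrent illness: "the child will be withdrawn from the study if any other illness arises during the treatment period that could influence study outcomes".
- Personal issues: "if a participant experiences personal issues that prevent continuation of therapy and are likely to affect the study results, they will also be withdrawn".

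Study Design lists six treatment-period visits: "follow-up assessments on the 15th, 30th, 45th, 60th, 75th, and 90th day". A further visit follows on day 180. The primary outcome is BMI, and the design is equivalence.

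Statistical Analysis compares mean changes between groups by t test or Mann-Whitney test, and also names analysis of covariance. In its sentence on residual efficacy at 180 days it adds that "mixed-effects models will handle missing data or variability across time points". The sample size section (Participants) ends: "With 10% dropout=43 each=86 samples". Enrolment is then raised to 44 per arm. The article does not say whether an excluded child is still measured at day 90 or stays in the analysis.

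**The concern.** A child with BMI at baseline and day 90 who misses, say, only day 45 has everything a comparison of change needs, yet is put out of the study. A child who worsens is put out for a reason that may be related to the outcome. Either way, the children who remain are no longer the groups that were randomised.

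This matters more than usual in an equivalence trial. If children who do badly are lost, the arm with more of them loses more, the observed difference narrows, and the bias favours the conclusion the trial hopes to reach. Attrition by rule also uses up the dropout allowance. Finally, a plan that removes every child with a missed treatment visit fits poorly with a plan to model missing data. BMI that was never measured at day 90 cannot be recovered at the analysis stage.

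**Working it through.** **1. The plan's own figures.** Inputs from Participants: SD 0.86, δ 0.57, 39 per arm, 10% dropout.
- Dropout step: 39 × 1.10 = 42.9, so 43 per arm, as stated. Dividing instead, 39 / 0.90 = 43.3, so 44, the number finally enrolled.
- Base size: the printed expression 2 × (1.96 + 0.84)² × 0.86² / 0.57² gives 35.7, so 36 and not 39. The figure 39 does match two one-sided tests (TOST) at 5% each with 80% power and 0.57 as the margin: 2 × (1.645 + 1.282)² × 0.86² / 0.57² = 39.0. That mismatch is a separate matter. Below, 39 is the target and 0.57 is read as the margin.

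**2. Missed-visit rule, independent misses.** Let p be the chance of missing one visit (assumed, since the article gives none). Share removed over six visits = 1 − (1 − p)⁶.
- 10% is reached at p = 1− 0.9^(1/6) = 1.74%.
- 44 falls to 39 per arm at p = 1 − (39/44)^(1/6) = 1.99%.

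TOST power = 2Φ(0.57/SE − 1.645) − 1, with SE = 0.86 × √(2/n) and true difference 0.

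| p per visit | removed | left per arm (of 44) | TOST power |
|---|---|---|---|
| 1% | 5.9% | 41.4 | 83% |
| 2% | 11.4% | 39.0 | 80% |
| 3% | 16.7% | 36.7 | 77% |
| 5% | 26.5% | 32.3 | 69% |
| 10% | 46.9% | 23.4 | 47% |

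For 5%: SE = 0.86 × √(2/32.3) = 0.214; 0.57/0.214 = 2.67; 2Φ(1.02) − 1 = 0.69. Keeping 39 per arm would need 39 / 0.735 = 53.1, so 54 per arm.

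**3. Misses clustered within children.** A beta-binomial model with within-child correlation ρ from 0.1 to 0.5 (assumed) gives fewer removals:
- p = 2%: 9.2% down to 4.8%
- p = 5%: 21.7% down to 11.7%
- p = 10%: 39.4% down to 22.3%

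Losses from worsening, illness and personal issues come on top in every case.

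**4. Worsening rule.** Assume that BMI change is normal with SD 0.86, that the true difference is 0.57, that a rise above a cut-off c counts as worsening, and that such children are not analysed. The mean among those kept is μ − 0.86 × φ(b)/Φ(b), with b = (c − μ)/0.86. Both c and the mean changes are assumptions.

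| mean changes (kg/m²) | cut-off | excluded | observed difference |
|---|---|---|---|
| +0.07 and −0.50 | 0 | 53%, 28% | 0.24 |
| 0 and −0.57 | +0.5 | 28%, 11% | 0.34 |
| −0.43 and −1.00 | 0 | 31%, 12% | 0.33 |
| −0.50 and −1.07 | +0.5 | 12%, 3% | 0.44 |
| −0.93 and −1.50 | +0.5 | 5%, 1% | 0.50 |
| −1.00 and −1.57 | +0.5 | 4%, 1% | 0.51 |

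The shift is towards no difference in every row. Its size depends on how many children worsen.

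**5. The two sections side by side.** If every child with a missed treatment visit is out, those who remain have complete data to day 90. What is left for the mixed model is a missing day-180 value and, if they are retained, the early visits of children removed part-way.

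**The case against.** Several points on the other side stand.

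- A reader might infer that the 10% allowance will be overrun. The documents do not support that as fact. They give no attendance rate; at 1% per visit this rule alone stays inside the allowance, and so does 2% if misses cluster. With 44 enrolled, 2% independent misses still leave 39.0 per arm. Guardian education and calls or text messages reminding families about diet and exercise may also help attendance.
- A reader might infer that both rules bias towards equivalence. For missed visits the direction depends on why visits are missed, which the article cannot tell us. The smaller sample widens the interval, which makes equivalence harder to show.
- Worsening is not defined in terms of BMI. The wording about care until symptoms subside can be read as a clinical safeguard. The cut-offs above are illustrative, and where both arms improve well the shrinkage is modest.
- A reader might call the missing-data sentence a flat contradiction. It sits in the 180-day analysis, while the visit rule covers only the treatment period, so the two can be read together.
- Leaving the study is not the same as leaving the analysis, and an analysis set may be defined in a fuller document.

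The last point does not remove the problem. Taken as written, a child out of the study has no later BMI collected, and no choice of analysis set restores it. The exclusion rules are stated in the article; they are not details left for elsewhere.

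**Conclusion.** The concern holds in a bounded form. The article removes randomised children for a single missed visit out of six, for undefined worsening, and for other reasons judged likely to affect results. This loses usable BMI data and weakens the randomised comparison.

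Bias towards equivalence is supported for the worsening rule only, and only if worsening tracks BMI and excluded children are not analysed; a true 0.57 then appears as roughly 0.24 to 0.51. The dropout allowance is exceeded if more than about 1.7% of visits are missed independently (2.0% for 44 falling to 39 per arm), or at a higher rate with clustering. At 5% per visit the loss is 26% if independent and about 12% to 22% if clustered. The independent case leaves about 32 per arm and 69% power. The exclusion rules and the mixed-model sentence are in tension and must be reconciled.

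**What to change.** - Delete the rule that a missed follow-up excludes the child, and record the visit as missing.
- Separate stopping study treatment from leaving the study. The clinical care described in Ethical Considerations, and the decision to stop treatment, stay as they are. Measurement of day-90 and day-180 BMI continues unless consent or assent is withdrawn.
- Analyse all randomised children as randomised for the day-90 comparison, using the mixed model already named, and state that it covers treatment-period visits as well as day 180. Because children who worsen go on to conventional care, say explicitly that their BMI is used regardless of that care.
- Report a per-protocol analysis (missed visits, discontinuation) alongside, and state beforehand how the two bear on the equivalence conclusion. Requiring both to agree is one common convention.

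The cost is protocol wording, a few off-treatment weight and height measurements at visits already scheduled, and one extra analysis set. Children already removed under the present rule should be invited back for the remaining measurements where consent allows.

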
## Results

In April 2024, the randomized controlled study got underway. Since participants may be in the study at any time, our goal is to complete the research by May 2025. Any significant changes to the protocol will be posted on ClinicalTrials.gov. The study’s findings will be disseminated through publications.

## Discussion

### Principal Findings

Childhood obesity has been rising in the past 3 decades. Its prevalence is increasing both in the higher socioeconomic groups as well as lower socioeconomic groups [7]. The short- and long-term associations between overweight and a range of adverse health-related outcomes are well established and raise the level of importance for understanding overweight as a major public health concern for children and adolescents. Lack of physical activities and uncontrolled dietary habits are the root causes of higher incidence rates of overweight in children. Nowadays, increased screen time is also contributing to this problem. It increases motivated responses to food intake and snacking behavior among children and adolescents [47,48].

Vachaharidradi Gana is a herbal compound mentioned in Ayurvedic classics that is effective in the reduction of excessive fat by its Kaphamedohara property. In the case of Sthaulya [49], there is an abundance increase in Kapha and Medo Dhatu (fats). These Dhatu are predominant in Jala (water element) and Pruthvi (earth element) Mahabhuta. The contents of the Vachaharidradi Gana are opposite in characteristics to that of Kapha-Medodhatu. Thus, it is expected to break the etiopathogenesis of Sthaulya if administered to children with overweight.

Dietary changes are directly linked to weight loss. Fixed lunch and dinner times, low-fat meals, fiber-rich vegetables, and reduced frequency and amount of food are advocated in the management of Sthaulya [50]. However, it may be a matter of concern to maintain the reduced weight for a longer period. Hence, with the addition of diet control and medicine administration, it is essential to add some behavioral changes too. Behavioral modifications are found to be useful for good weight maintenance. In Ayurveda, it is aimed at exercises or yogic practice. Yogic practices involve stretching and relaxation of various muscles steadily, which breaks down triglycerides and mobilizes fatty acids. Yogic practices also act synergistically with diet restrictions in Sthaulya [51,52]. Yoga practices such as Suryanamaskara can be an enjoyable and engaging way to encourage physical activity among children, fostering self-discipline, which could extend to healthier eating habits and more structured activity levels with improved mental well-being. While specific studies on Suryanamaskara for childhood obesity are limited, studies on general yoga practices for children have shown promising results in reduced BMI and waist circumference and are equally effective as the standard weight management for BMI reduction in the pediatric and adolescent age group [53-55]. One-hour yoga session for 12 weeks comprising Suryanamaskara, asanas, pranayama, and meditation in adolescent girls having polycystic ovarian syndrome showed significant alterations in blood glucose, insulin, and lipid levels [56]. A review paper on Suryanamaskara concluded that if practicing Suryanamaskara is initiated in children at the age of 7-8 years, it helps them grow better not only physically but also with great mental health [36]. In this study, the daily performance of Suryanamaskara is advocated in the form of a yogic practice. Hence, it was hypothesized that the Vachaharidradi Gana Vati along with diet restriction and Suryanamaskara will help in the reduction of the weight and BMI of children with overweight.

Navak Guggulu, on the other hand, is a control drug, whose efficacy has been proven in obesity and hyperlipidemia. The addition of diet restriction and Suryanamaskara will add further to its proven efficacy. The effect of combined interventions in both groups is expected for a sustained period even after the stoppage of the medicines.

This is the first study in which Suryanamaskara is advocated as part of a multidimensional treatment modality for reducing weight and BMI in children. It will further elaborate on the benefits of Suryanamaskara in children. It is expected that this modality will also help to lower the raised values (if any) of lipid profiles and the signs and symptoms of Sthaulya.

Children do not tolerate dosage that is in powdered form; therefore, changing the powder form of a medication into a tablet makes dosage calculations simple and makes sure that the recommended quantity is administered. Further, the double blinding will help in controlling performance bias and ascertainment bias that might inadvertently sweep into the study.

Being overweight deteriorates cognitive functioning in children while it adversely affects them psychologically. Children with overweight show behavioral disorders, a high emotional nature, damaged self-awareness, and low self-evaluation and demonstrate unhappiness. It is a cause of social concern [57,58].

Considering all these factors, treating children with overweight and preventing them from becoming obese are of utmost importance. The available research on overweight in children is limited. Given the multifactorial etiopathogenesis of children with overweight, drug administration alone will not be sufficient for treatment. Therefore, a multidimensional approach to treating children with overweight will be practiced in this study. Positive study findings may implicate a feasible, promising, noninvasive, and affordable intervention for managing children with overweight, which also offers sustainable holistic lifestyle modifications and positive psychological changes. This study could enhance the scientific credibility of Ayurveda in managing childhood obesity and support its integration into modern health care guidelines. The use of locally available, affordable herbs like Vachaharidradi Gana Vati could make obesity management more accessible in low-income settings.

### Limitations

The parents may resist accepting the fact that their children with overweight need treatment. It may be difficult to monitor whether the children follow diet restrictions and Suryanamaskara for a longer period. Additionally, as this is a PhD study without external funding, the sample size is relatively small.

### Potential Avenues or Strengths of Study

Ayurveda herbal medicines have great potential or impact to cure the disease naturally without any side effects. The Ayurvedic diet and lifestyle recommendations can be added as multidimensional aspects of the conventional treatment modality.

This research trial is planned to know the Kaphamedohara effect of the classical formulation by administering it orally to children with overweight. The positive outcome of the study will facilitate the commercialization of the product, Vachaharidradi Gana Vati. Further, the medicines used in the study can be patented and made copyrighted later and publicized for the benefit of the population. Large-scale, multicentric RCTs can be conducted to test the effect of Vachaharidradi Gana Vati on children with overweight and also children with obesity. Such a trial can be conducted in adults and young children (aged 3-9 years) as well. Longitudinal studies could evaluate the long-term impact of Ayurvedic interventions on childhood obesity, focusing on not only weight and BMI management but also quality of life, psychological well-being, and prevention of obesity-related diseases in adulthood.

### Conclusions

This research will be useful to provide new insight into the effectiveness of the Ayurveda pharmacological approach in treating obesity in children. The results will guide evidence-based multimodality in treatments aimed at changing lifestyle behaviors in children with obesity, thus reducing social stigmatization in them.

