## Abstract

**Background:**

Childhood obesity is a lifestyle-oriented disorder, which may lead to many comorbidities such as hypertension, coronary diseases, increased incidence of diabetes, and metabolic syndromes. Lack of diet control and increased screen time specifically after the COVID-19 pandemic among children and adolescents are the major reasons for this rising global concern. Despite various campaigns being carried out to lessen the rising rates of childhood obesity, the objectives have not yet been achieved. Ayurveda offers a multidimensional modality in managing children with overweight. The purpose of this study is to evaluate the combined efficacy of Ayurvedic medicine administration, diet restriction, and Sun Salutation. Navak Guggulu is a herbo-mineral compound already proven for its antiobesity action. Vachaharidradi Gana mentioned in Ayurvedic classics is a group of herbs, which are Kaphamedohara and Karshana. Ayurveda also emphasizes the importance of diet and physical activities for the treatment of obesity. The interventions together may help in promoting a healthy weight, improving metabolism, and reducing fat accumulation. So, in this study, the efficacy of Vachaharidradi Gana Vati will be compared with Navak Guggulu to treat children with overweight in addition to diet restrictions and Sun Salutation.

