Overweight or obesity is characterized by increased weight, increased weight for height, and raised BMI [10]. Recently, new Indian standards have been notified, and new 5- to 17-year charts of BMI for boys and girls have been published by the Indian Academy of Pediatrics. According to that, the BMI cutoffs for overweight and obesity in children are defined at 23 and 27 kg/m^2^, respectively (Indian Academy of Pediatrics 2015) [11]. Obesity is a risk factor for numerous noncommunicable diseases, including type 2 diabetes mellitus, asthma, joint pain, and multiple health conditions [12-16]. It frequently carries a high risk of early mortality and significant disability [17]. Children with overweight are more likely to experience cognitive developmental issues and are more likely to become adults with obesity. Obesity prevention should begin in childhood. According to the WHO expert constitution, on average, obesity reduces life expectancy by 6-7 years in adults [18-20].

Despite various campaigns being carried out to lessen the rising rates of childhood obesity, the objectives have not been achieved. The main causes include lack of awareness, poor adherence to balanced diet guidelines, and the absence of comprehensive policies to address this hidden epidemic [21]. It has become the need of the hour to recognize children with overweight and treat them as early as possible.

According to Ayurvedic classics, Sthaulya can be correlated with overweight or obesity. It is a Santarpanajanya Vyadhi [22], which means the disease caused due to excessive intake of food and decreased physical activities. In Ayurveda, the management of Santarpanajanya Vyadhi is a multidimensional modality. It includes medicine administration, Nidanaparivarjana [23] (avoidance of causative factors), diet control, and Vyayama (physical exercise). Ayurveda offers various medicines for the treatment of Sthaulya. Navak Guggulu is a well-known polyherbal compound containing guggulu (*Commiphora mukul* Linn) as the main ingredient. This compound is reported for its antiobesity action [24-27]. It has also been studied in the management of hyperlipidemia [28]. Though it is a proven drug, the availability of pure guggulu is a difficult task day by day. There is a scarcity of pure guggulu, and it is a tedious job to purify guggulu for oral administration, as the available guggulu contains many impurities.

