### Inclusion Criteria

The inclusion criteria are as follows: participants irrespective of gender, religion, and socioeconomic status, age group between 10 and 16 years with signs and symptoms of overweight (Sthaulya) due to exogenous causes, participants with BMI ≥23 and <27 kg/m^2^, and parents who are willing to provide written informed consent for their children to be included in the study.

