### Exclusion Criteria

The exclusion criteria are as follows: children having BMI <23 and ≥27 kg/m^2^, children aged <10 years and those aged >16 years, and children who are overweight due to endocrine causes. Children experiencing severe systemic illnesses like hypertension, asthma, diabetes mellitus, nephrotic syndrome, kwashiorkor, and congestive cardiac failure having anasarca condition are overviewed as overweight.

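### The stated conclusions reach children with obesity, whom eligibility excludes, and the stated purpose and objectives credit a lifestyle package that both arms receive alike

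*Protocol article*

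**What the plan says.** **Population.** The Introduction (Background) states that "the BMI cutoffs for overweight and obesity in children are defined at 23 and 27 kg/m^2^, respectively". The Inclusion Criteria admit "participants with BMI ≥23 and <27 kg/m^2", and the Exclusion Criteria remove "children having BMI <23 and ≥27 kg/m^2". Study Design repeats the same range. The Conclusions, printed in the Abstract and again at the end of the article, nevertheless announce "new insight into the effectiveness of the Ayurveda pharmacological approach in treating obesity in children" and add that "The results will guide evidence-based multimodality in treatments aimed at changing lifestyle behaviors in children with obesity".

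**Components.** Under Study Design, "Both groups will receive counseling to perform 12 Suryanamaskara (Sun Salutation) per day and adhere to the dietary restrictions". Table 1 shows the arms differing only in which tablet is taken. The Abstract (Background) says that "The purpose of this study is to evaluate the combined efficacy of Ayurvedic medicine administration, diet restriction, and Sun Salutation", and the Discussion (Principal Findings) says of the study that "It will further elaborate on the benefits of Suryanamaskara in children".

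**Operative text.** Primary objectives 1 and 2 are to evaluate, one arm at a time, the efficacy of each tablet given with diet restriction and Sun Salutation. Statistical Analysis assigns paired tests (or Wilcoxon signed rank tests) of pre- against post-treatment values to within-group efficacy. Primary objective 3 is the comparison between the two arms.

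**The concern.** There are two separate mismatches between what the article says it will conclude and what the design can show.

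The first concerns the population. The conclusion names a group that the eligibility limits keep out, so applying the results to it would be extrapolation across a boundary the trial set for itself.

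The second concerns attribution. Where everyone is assigned the same lifestyle programme, a fall in BMI within an arm cannot be credited to that programme, or to tablet and programme together, because nobody goes without. Yet package efficacy is a primary objective with a planned significance test. A report that followed the plan could present a small pre-post p value as proof that the package works. The Discussion links positive findings to health care guidelines and to commercialisation of a product for children, so the reach of the claim matters.

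**Working it through.** The article gives no figure for this point, so there is none to reproduce. The check sets its statements side by side.

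**Step 1: population.**

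| Item | BMI range (kg/m²) | Source |
|---|---|---|
| Overweight | from 23, below 27 | Introduction, Background |
| Obesity | 27 and above | Introduction, Background |
| Enrolled | 23 to below 27 | Study Design; Inclusion and Exclusion Criteria |
| Named in the conclusion | obesity | Conclusions (Abstract and main text) |

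The enrolled range and the obesity range do not overlap. If eligibility is applied as written, 0 of 88 children have obesity at entry. Some may cross 27 during follow-up, but they would not have been randomised as children with obesity.

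**Step 2: what the randomised contrast contains.** In a simple additive picture, let T_A and T_B be the effects of the two tablets, L the effect of diet restriction plus Sun Salutation, and G everything else that moves BMI between visits (growth, time, regression to the mean after selection on BMI). The expected changes from baseline are:

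- Arm A: T_A + L + G
- Arm B: T_B + L + G
- Difference: (T_A + L + G) − (T_B + L + G) = T_A − T_B

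L cancels. If the tablets act differently in the presence of the lifestyle programme, the difference becomes the tablet contrast given that programme. It still carries no information on L, or on T + L.

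**Step 3: what the within-arm change contains.** The two arm means give two equations in four unknowns (T_A, T_B, L, G). The package effect T + L can be separated from G only if G is known or assumed to be zero. A paired test against no change in effect assumes G = 0. The article offers no basis for that in children aged 10 to 16 who are selected on BMI and followed for 90 and 180 days. It gives no figure for G, so the possible bias cannot be sized from it.

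**Step 4: exposure.** All 88 children (44 + 44) are assigned the diet restriction and Sun Salutation, and none is without them. The Limitations section adds that adherence to both may be hard to monitor. It does not mention the missing comparator.

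**The case against.** The strongest reply is that this is loose framing around a trial whose working parts are already correctly limited. The hypotheses, eligibility, randomisation and between-group objective all concern overweight children and two tablets, and no obesity subgroup or test of Sun Salutation is planned. The article also uses one Ayurvedic term for both overweight and obesity, speaks of keeping overweight children from becoming obese, and leaves children with obesity to later trials (Potential Avenues or Strengths of Study). An attentive reader could correct the wording unaided.

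Much of this is fair. It does not dispose of the point, because the article's own cut-offs separate the two conditions and its conclusion names the excluded one. On the lifestyle side the problem also goes beyond framing: package efficacy is written into primary objectives 1 and 2 and tied to paired tests.

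Three stronger readings are tempting and are not supported:

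- *That there will be no data on the package.* Pre-post change will be recorded in each arm. What is missing is a comparator.
- *That the Conclusions themselves claim a Sun Salutation benefit.* They refer to multimodal treatment and lifestyle behaviours without naming it. The explicit statements are in the Abstract (Background) and the Discussion (Principal Findings).
- *That the design is broken.* The shared lifestyle programme is a legitimate common background for comparing the tablets, and that comparison is not harmed by it.

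**Conclusion.** The point holds as over-reach in the stated conclusions, the stated purpose and two primary objectives. By the article's own definition none of the 88 planned children has obesity at entry, so the trial gives no direct evidence in that group. All 88 are assigned the same diet restriction and Sun Salutation, so the randomised comparison is silent on those components and on the package. The within-arm change is uncontrolled and cannot carry an efficacy conclusion.

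This assumes that the eligibility limits are applied as written and that the lifestyle advice is delivered alike in both arms, as Study Design says. No sample size, error rate or between-arm estimate changes. What changes is what the trial may conclude.

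**What to change.** - **Conclusions (Abstract and main text):** limit the statement to children aged 10 to 16 with a BMI of 23 to below 27 kg/m², and to the comparison of the two tablets when both are given with diet restriction and Sun Salutation. Leave obesity to the later trials the article already proposes.
- **Abstract (Background) and Discussion (Principal Findings):** delete the claims about the package and about Sun Salutation, or mark them as uncontrolled description.
- **Primary Objectives and Statistical Analysis:** relabel objectives 1 and 2 and the within-group paired tests as descriptive change from baseline, leaving the between-group BMI comparison under objective 3 as the only efficacy conclusion.

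Editing the Abstract and Discussion alone would not be enough, because the package claim would survive as a primary objective. The change is wording only: arms, sample size, visits and data collection stay as they are. The cost is a narrower stated reach.
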